## Abstract

**Introduction:**

Encouraging the activation of brain repair mechanisms and fostering spontaneous functional recovery in stroke patients hold great promise for alleviating the global burden of this condition and allowing an extended therapeutic time window. Cell-based regenerative therapy (with mesenchymal stem/stromal cells, such as adipose-derived stem cells [ADSCs]) is particularly attractive considering its excellent safety profile, low immunogenicity after allogeneic application, and well-established functional benefits on stroke recovery in animal models. This study aims to assess the efficacy and safety effects of intravenous (IV) infusion of freshly cultured allogeneic ADSCs on recovery after ischemic stroke.

**Population and methods:**

RESSTORE is a multicentric, randomized 1:1 controlled double-blind clinical trial. Eighty patients will be enrolled in nine French stroke centers. The main inclusion criteria are ≥18 years of age, acute hemispheric ischemic stroke, and a National Institutes of Health Stroke Scale (NIHSS) score of ≥7, including a motor subscore of ≥3. According to the previous dose-escalation safety trial data, the maximum tolerated dose of 3 million ADSCs/kg was selected. IV infusion was performed within 10 days following stroke onset, with a follow-up over 2 years.

**Outcomes:**

The primary endpoint is the motor NIHSS subscore, computed as the sum of the upper limb, lower limb, and hand scores, measured 6 months after stroke onset to assess motor recovery. The secondary outcomes are the occurrence of death/serious adverse events, clinical scores (the detailed NIHSS scores, Montreal Cognitive Assessment scores, modified Rankin Scale scores, Aphasia Handicap Scores, Depression Intensity Scale Circles scores, Fatigue Scale scores, etc.), immune monitoring (for the first 30 patients), and multimodal biomarkers derived from diffusion and functional magnetic resonance imaging.

**Discussion:**

This study may provide some evidence for the effects of freshly cultured allogenic ADSCs IV infusion in subacute stroke that may help design a larger international randomized controlled trial.

**Clinical trial registration:**

https://clinicaltrials.gov/, identifier: NCT03570450.

## 1 Introduction

In the European Union, approximately 6 million people are impacted by stroke, with 1.1 million new cases reported each year. Despite experiencing some degree of spontaneous recovery, more than 60% of stroke survivors contend with lasting impairments, resulting in significant burdens for both patients and their families, with broader societal implications. The stroke burden is expected to increase due to the aging population, the sharp rise in diabetes, and obesity reaching a pandemic level (GBD 2019 Stroke Collaborators, 2021).

Current treatment options are limited in the acute phase to intravenous (IV) thrombolysis, mechanical thrombectomy, aspirin within 48 h, decompressive craniectomy for large strokes, a stroke care network for intensive care management, and neurorehabilitation. After experiencing a stroke, the majority of survivors still endure sensorimotor and cognitive disabilities, amplifying the stroke burden on rehabilitative care. Hence, the demand for treatments that extend beyond prevention and acute care to be effective is urgent. However, developing novel therapies requires a sophisticated understanding of stroke pathophysiology. It is well known that stroke damages not only neurons but also involves both brain cells and the surrounding extracellular matrix in a “glio-neurovascular niche” that interacts with the peripheral immune system (Detante et al., 2023). For these reasons, new therapies should target all these systems to perhaps avoid the failures of past clinical translational attempts to develop specific protective drugs (Dirnagl and Endres, 2014).

A promising approach involves activating brain repair mechanisms and fostering spontaneous functional recovery using regenerative therapies. A major advantage is the extended therapeutic window of up to days or months after stroke, making this treatment available to a much larger number of stroke patients. Cell-based regenerative therapies have emerged as attractive approaches for stroke (Detante et al., 2023; Boncoraglio et al., 2019). Various cell types and strategies have demonstrated significant improvement in experimental studies. Of particular interest are mesenchymal stem/stromal cells (MSCs), which can be easily derived from multiple sources, including adipose tissue (adipose-derived stem cells, ADSC). In addition, their excellent safety profile and low immunogenicity after allogeneic application may enable their use as an “off-the-shelf” therapeutic product (Toyserkani et al., 2017). Concerning the delivery route, IV cell infusion, a non-invasive, and safe method that provides a broad distribution of cells close to ischemic tissue, has immediate access to clinical applications.

Although a prior meta-analysis hinted at the potential benefits of cell therapy for stroke patients (Detante et al., 2017), individual clinical trials have yet to yield significant results (Hess et al., 2017; Moniche et al., 2023; Houkin et al., 2024). Several factors have been suggested, including the cell type and the timing of cell administration after a stroke, which may be influenced by the potential delay in *in vitro* amplification. Additionally, the targeted mechanisms of action—whether focusing on acute brain protection, delayed brain repair, trophic systemic transient effects, or graft survival and integration—could also contribute to the lack of significant results. Moreover, using freshly cultured stem cells instead of frozen stem cells can lead to better therapeutic outcomes by ensuring higher cell viability and functionality.

Utilizing global outcome measures (e.g., modified Rankin Scale [mRS], Barthel Index, and the EuroQOL) could contribute to the observed limited efficacy (Hess et al., 2017; Houkin et al., 2024). Intriguingly, although motor performance is frequently assessed in experimental studies to evaluate the effects of cell therapy, it is not commonly examined in clinical randomized controlled trials (RCTs). According to the results of a previous study (Jaillard et al., 2020), we hypothesized that quantitative motor behavior and functional magnetic resonance imaging (MRI) measurements may provide objective and accurate measures of outcomes, resulting in more sensitive detection of treatment effects.

Therefore, our aim was to design an RCT to assess the effects of freshly cultured ADSCs in patients with subacute stroke.

The optimal window after stroke for cell administration remains a debate. Because the expected trophic support is the main mechanism of MSC injections occurring days to weeks after stroke onset and considering the delay required for the production and delivery of freshly cultured cells (5–7 days), we targeted the 7–10 days following stroke onset to administer IV ADSCs in the RESSTORE clinical trial.

The RESSTORE clinical trial includes two phases. The first phase, 1a, a first-in-human trial, was a dose escalation safety study including 17 patients with an acute first-ever ischemic stroke to determine the highest well-tolerated, safe single IV dose of 1–3 million ADSC/kg administered 7–10 days after stroke onset. The RESSTORE 1a study was completed in 2022, showing no cell-related adverse events for all treatment doses (preliminary data) (Detante et al., 2022). Therefore, the highest dose of 3 million ADSC/kg was selected for the second phase of the study, RESSTORE 1b.

RESSTORE 1b, a RCT, started in October 2023. The primary objective is to assess the efficacy of IV 3 million ADSC/kg on motor recovery 6 months following stroke. The secondary objectives are to assess ADSC safety and efficacy using neurological and physiotherapy clinical scores and biological and multimodal MRI parameters.

## 2 Methods and analysis

### 2.1 Study design

RESSTORE 1b is a double-blind single-dose multicenter prospective RCT.

The study flowchart is presented in Figure 1.

**Figure 1 F1:**
[figure not shown]
Experimental flowchart of RESSTORE trial. ADSCs, adipose-derived stem cells; IV, intravenous; fMRI, functional magnetic resonance imaging; MRI, magnetic resonance imaging; NIHSS, National Institute of Health Stroke Scale; V^*^, visit number ^*^.

For each patient randomized in RESSTORE trial, seven visits are planned, from the inclusion (Visit 1) to the 2-year follow-up (Visit 7). The primary endpoint will be evaluated at 6 months (motor sub-score of the NIHSS). Safety and efficacy will be assessed by clinical scores and biological and multimodal MRI markers.

### 2.2 Patient population, inclusion, and non-inclusion criteria

This study will recruit 80 patients from 9 stroke comprehensive centers in France. The inclusion criteria are as follows: age ≥18 years, hemispheric ischemic stroke (>1.5 cm on 2 imaging slices, as determined by the first routine care brain imaging following stroke onset, either computed tomography scanner or diffusion-weighted MRI), no previous handicap, and the ability to follow a neurorehabilitation program. To assess ADSC efficacy, we target patients with moderate to severe stroke. Thus, eligible patients have a National Institute of Health Stroke Scale (NIHSS) score ≥7, with a motor sub-score (upper, lower limbs, and hand) ≥3, and no planned or performed decompressive craniectomy. IV thrombolysis and/or mechanical thrombectomy can be performed based on international guidelines.

All inclusion and non-inclusion criteria are listed in Table 1.

**Table 1 T1:** Inclusion and non-inclusion criteria.

**Inclusion criteria**
Subjects will be eligible for the study if they meet all the following criteria: 1. Male or female >18 years old. 2. Hemispheric ischemic stroke (>1.5 cm on 2 imaging slices, determined on the first routine care imaging, i.e., CT scanner or diffusion-weighted MRI) admitted to the stroke unit within the first 24 h after stroke onset. 3. Patient must be included within the first or second day after stroke onset (signature of informed consent and randomization; i.e., between 24 h and 48 h from stroke onset) and must be able to receive investigation treatment within the first 10 days. 4. NIHSS score ≥7, including motor score (upper and lower limbs and hands) ≥3. 5. No decompressive craniectomy procedure (planned or performed). 6. Patient able to follow a rehabilitation program. 7. Modified Rankin Scale = 0 before stroke onset. 8. Obtained signed informed consent from the patient or legally acceptable representative. 9. Negative pregnancy test for women of childbearing age.
**Non-inclusion criteria**
Subjects will not be eligible for the study if they meet any of the following: 1. Contra-indication for MRI (*contra-indication to gadolinium is NOT a non-inclusion criterion but it is a contra-indication to optional injected MRI*). 2. Coma (score of 2 or more on item 1a of the NIHSS related to awareness). 3. Evidence on neuroimaging (CT or MRI) of a brain tumor, cerebral edema with midline shift and a clinically significant compression of ventricles, cerebellar or brainstem infarction, or subarachnoid hemorrhage, or intracerebral parenchymal hematoma (*petechial small hemorrhages, defined as Heidelberg Bleeding Classification grade HI-1and HI-2, are NOT a non-inclusion criteria*). 4. Severe leukoaraiosis (Fazekas scale = 3 for periventricular lesions). 5. Previous documented stroke. 6. Active endocarditis, pneumonia, AIDS, active hepatic disease due to HBV, or HCV (*a controlled infection is NOT a non-inclusion criterion*). 7. Active inflammatory and/or autoimmune diseases (such as Crohn's disease, lupus, rheumatoid polyarthritis, renal, or liver immune pathology). 8. History of cancer. 9. Preexisting dementia. 10. A health status, any clinical condition (e.g., short life expectancy or coexisting disease), or other characteristic that precludes appropriate diagnosis, treatment, or follow-up in the trial. 11. Surgical or endovascular procedure planned in the following 3 months. 12. Pregnancy/breastfeeding (women of childbearing age should have a negative pregnancy test prior to inclusion). 13. Patients who are participating in another therapeutic trial or who have previously participated in a biotherapy trial. 14. Non-membership to a social security scheme. 15. Inability or unwillingness of the individual or their legal guardian/representative to provide written informed consent, according to national regulations. 16. Person deprived of liberty by judicial order 17. Person under guardianship or curatorship.

CT, computed tomography; MRI, magnetic resonance imaging; NIHSS, National Institutes of Health Stroke Scale.

### 2.3 Treatment and intervention

According to the advice from the adjudication committee and the Data Safety Monitoring Board (DSMB) about the data from the dose-escalation previous study (RESSTORE phase 1a), the maximum tolerated dose of 3 million ADSC/kg has been selected.

As an advanced therapy medicinal product (ATMP), the freshly cultured allogeneic ADSCs are derived from the lipoaspirate of voluntary and informed healthy donors. ADSCs are provided according to the flowchart shown in Figure 2 by two distinct ATMP manufacturing units (EFS Auvergne Rhône Alpes, Grenoble/St-Ismier, France, and EFS Bourgogne Franche-Comté, Besançon, France) certified by EU competent authorities.

**Figure 2 F2:**
[figure not shown]
Flowchart of adipose-derived stem cells (ADSCs) production. DP/IMP, drug product/investigational medicinal product.

Freshly cultured allogeneic ADSCs are produced in a 1-week step, from a full-qualified working cell stock (WCS) issued from a unique healthy donor of adipose tissue.

A single IV infusion (placebo or ADSCs) is administered over 1 h (5 mL/min) in the stroke unit. During the infusion, the bag is regularly mixed to maintain the cells in suspension. Placebo corresponds to the vehicle media: glucose, human serum albumin, and ringer lactate. It is delivered by each ATMP manufacturing unit into an overwrapped packaging similar to that of the cell suspension. Patients, investigators, medical, nursing, and physiotherapy staff are blinded to the treatment assignment.

### 2.4 Sample size calculation

Assuming a mean NIHSS motor subscore of 3.5 in the control group and a common standard deviation of 2, a sample size of 39 patients per group achieves 90% power to reject the null hypothesis of equal means between the two groups, with a significance level (alpha) of 0.05 using a two-sided two-sample equal-variance *t*-test. We propose to include 40 patients per group in case technical issues occur with treatment delivery.

Eighty patients (40 in the placebo group and 40 in the treatment group) will be enrolled. We plan to include one patient per month per center, based on the inclusion criteria and the number of patients admitted to our stroke centers.

### 2.5 Randomization procedures

The randomization sequence has been generated using a computer before the study implementation. We use a dynamic allocation method based on age, severity (NIHSS score), side of infarction, recanalization procedure (thrombectomy and/or thrombolysis), and center. We randomize patients in a 1:1 ratio to receive an IV infusion of placebo or 3 million ADSC/kg within 10 days after stroke onset.

### 2.6 Follow-up

As shown in Figure 1, follow-up visits are scheduled at 2 weeks, 3 months, 6 months, 1 year, and 2 years following stroke to assess clinical scores and collect standard blood tests. Rehabilitation measures are assessed at 2 weeks, 6 months, and 1 year by a physiotherapist to independently assess patients' sensorimotor recovery. A multimodal MRI is performed at baseline and 6 months following stroke for safety and efficacy assessment.

### 2.7 Primary outcome

The primary efficacy outcome is the motor sub-score of the NIHSS, computed as the sum of the upper limb, lower limb, and hand scores, measured over time from baseline to 6 months visits in the ADSC group compared to the placebo group.

### 2.8 Secondary outcomes

*Second*ary outcomes include the following:

- Safety outcomes: This will involve monitoring for mortality and adverse events, specifically focusing on allergic reactions occurring within the first 24 h following treatment infusion, clinical perturbations (e.g., recurrent stroke and thromboembolic disease) occurring within the first week following infusion, and blood test abnormalities (e.g., hepatic cytolysis and leukocytosis). Additionally, MRI changes on T_1_ and Fluid-attenuated inversion recovery (FLAIR) images will be assessed, along with immunomonitoring for cross-reaction between host and allogeneic products and the presence of anti-Human Leukocyte Antigen (HLA) antibodies.- Behavioral measures using clinical and rehabilitation scores are to be collected from baseline to the 2-year follow-up visit. Clinical measures include the NIHSS, detailing each item, including a “hand motricity” assessment; a modified Rankin Scale (mRS) score, an Aphasia Handicap Score, a Montreal Cognitive Assessment score, a Depression Intensity Scale Circles score, a Fatigue Scale score, a Work and Social Adjustment Scale score, a Euro-Quality of Life 5-level visual analogue scale (EuroQol EQ5 VAS) score, and a 10 m walking test score. Rehabilitation measures include the motor part of the Fugl–Meyer score to assess sensorimotor recovery, the Postural Assessment for Stroke Scale for postural control evaluation, and the Ashworth Scale for spasticity assessment.- The brain MRI protocol includes T_1_-weighted and FLAIR sequences to assess safety, stroke lesion side and volume, and cortical thickness; diffusion sequences to assess white matter micro-structural alterations; and motor task-related functional MRI activity to assess the effects of ADSC compared to placebo from baseline to 6-month follow-up (Jaillard et al., 2020). Additional optional MRI sequences include magnetic resonance angiography (MRA) and arterial spin labeling perfusion; multi-parameter quantitative brain MRI maps to assess axon, myelin, iron, and water concentration of lesioned brain tissue; and exploratory magnetic resonance (MR) fingerprinting sequence to compute relaxometry maps, cerebral blood volume, and brain oxygenation maps (Christen et al., 2014). MRI biomarkers will also be used to improve our understanding of brain repair mechanisms and the effects of ADSC therapy on post-stroke brain remodeling.- An immunomonitoring study is performed in the 30 first patients at baseline and 3-month follow-up to assess safety and explore the immunomodulation effect of ADSCs.

### 2.9 Statistical analysis

All primary and secondary outcomes will be analyzed in the intent-to-treat population. Additional analysis will be performed using a modified analysis set (all patients who are randomized and still alive at 6 months + 1-week post-randomization) and in the per-protocol population (all randomized patients who received the complete assigned study treatment and complied with all inclusion and non-inclusion criteria). A safety analysis will be performed on the whole study population, comparing all randomized patients who received any amount of the planned ADSC treatment to patients who received a placebo.

The primary effectiveness outcome is the change in the NIHSS motor sub-score at 6 months. The change in the NIHSS motor sub-score is a quantitative value and will be analyzed using a mixed model for repeated measures including patients as a random effect and as fixed effects: baseline NIHSS motor score, visit, treatment, and interaction between treatment and visit. Gender and stratification variables for randomization (age, recanalization procedure, lesion side, and center) in the model will be adjusted.

Comparisons between treated and control groups will be conducted using Student's *t*-test or the Mann–Whitney *U* test for continuous outcomes, the chi-squared test or Fisher's exact test for binary outcomes, and the Mantel–Haenszel chi-squared test or the Cochran–Mantel–Haenszel test for ordinal outcomes.

The treatment effect on the change from baseline for secondary efficacy behavioral outcomes will be tested, as for the primary outcome, using mixed models for repeated measures. At the 2-year follow-up visit, the mean change from baseline between treatment groups will be compared to the minimum clinically important difference for each score, provided that such data are available. An alternative analysis will categorize scores using published or specific cutoff scores, which will be reported as part of the study results.

A shift analysis of the mRS scores will be considered using an ordinal logistic regression.

For MRI biomarkers, the same primary analysis of treatment effect on change from baseline will be performed.

To account for multiple tests, a false discovery rate approach will be used to control the proportion of false hypotheses rejected for MRI data or blood biomarkers.

Safety outcomes occurring in the first 24 h and during the study will be described by the treatment group and compared using summary statistics. The analysis will utilize various modeling frameworks, including logistic regression for event occurrence, time-to-event analysis, and count data regressions for recurrence or multiple events.

Multivariate statistical techniques (factor analysis, cluster analysis, and discriminant analysis) or more advanced methods will be performed on the data collected for the 30 first patients at baseline and the 3-month follow-up to identify the effect of treatment on the immunomonitoring study.

Unless stated, if the *p*-values for multiple tests are not adjusted, 95% confidence intervals will be used as a measure of precision. All statistical analysis will be performed using SAS (SAS Institute Inc., Cary, NC, USA), or R software (R foundation, Vienna, Austria).

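### Read literally, the primary model's random patient effect assumes equal variance at every visit and can misstate the 6-month standard error; an unstructured covariance avoids this at little cost

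*Protocol article*

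**What the plan says.** Section 2.9 states: "The primary effectiveness outcome is the change in the NIHSS motor sub-score at 6 months". The analysis is "a mixed model for repeated measures including patients as a random effect", with fixed effects "baseline NIHSS motor score, visit, treatment, and interaction between treatment and visit", adjusted for gender and the stratification variables. No residual covariance structure is named.

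Section 2.7 describes the outcome as followed from baseline to the 6-month visit. Section 2.6 says that "follow-up visits are scheduled at 2 weeks, 3 months, 6 months, 1 year, and 2 years following stroke". The post-baseline visits up to the primary time point are therefore 2 weeks, 3 months and 6 months.

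The only variability figure is in section 2.4, "a common standard deviation of 2". It is common to the two groups and attached to the motor subscore. No SD or correlation by visit is given.

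**The concern.** The section does more than leave the covariance open. It lists the fixed effects and names one source of within-patient dependence, a patient effect. An analyst who codes that sentence as a random intercept with default residuals assumes one variance for all visits and one correlation for all pairs of visits.

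The primary comparison is at one visit, 6 months. Under that model its standard error is built from all three visits. If patients diverge as some recover and others do not, the early visits have smaller variance and pull the standard error down. If scores converge, they pull it up. The confidence interval and type I error of the trial's primary test then depend on an assumption that the article does not support with any figure.

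**Working it through.** **The plan's own figure.** Section 2.4 says that "a sample size of 39 patients per group achieves 90% power", with SD 2 and two-sided alpha 0.05, but gives no treatment difference, so 39 cannot be derived from the stated inputs alone. Solving the noncentral-t power for 39 per group gives a difference of 1.487. With an assumed difference of 1.5, power is 0.905 at 39 per group and 0.897 at 38, so 39 is consistent with 1.5. This is a t-test calculation and does not depend on the present point.

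**Standard error under the literal reading.** Take 3 visits, n = 40 per arm, complete data, and treatment by visit in the model.

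- The estimated 6-month difference is the difference of the 6-month means, whichever covariance is used.
- Its true standard error is SD6 × √(2/40). For SD6 = 2 this is 2 × 0.2236 = 0.447.
- Under a random intercept, the between-patient mean square (MSB) estimates σe² + 3σb² and the within-patient mean square (MSW) estimates σe². The total variance σb² + σe² is therefore estimated by (MSB + 2·MSW)/3, which is the mean of the three visit variances.
- Hence the ratio r = model SE / true SE = √(mean visit variance / 6-month variance), and type I error ≈ 2 × [1 − Φ(1.96 r)].

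Only relative SDs enter r. All the visit SDs below are assumptions.

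| SD at 2 wk / 3 mo / 6 mo | Mean variance | r | Type I error |
|---|---|---|---|
| 2 / 2 / 2 | 4.00 | 1.00 | 5.0% |
| 1.5 / 1.8 / 2 | (2.25 + 3.24 + 4)/3 = 3.16 | 0.89 | 8.1% |
| 1.2 / 1.7 / 2 | (1.44 + 2.89 + 4)/3 = 2.78 | 0.83 | 10.3% |
| 1.0 / 1.6 / 2 | (1 + 2.56 + 4)/3 = 2.52 | 0.79 | 12.0% |
| 2.5 / 2.2 / 2 | (6.25 + 4.84 + 4)/3 = 5.03 | 1.12 | 2.8% |
| 2 / 2 / 1.6 | (4 + 4 + 2.56)/3 = 3.52, against 2.56 | 1.17 | 2.2% |

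For 2.5 / 2.2 / 2, power at an assumed difference of 1.5 falls from Φ(1.5/0.447 − 1.96) = 91.8% to Φ(1.5/0.447 − 1.96 × 1.12) = 87.6%.

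**Simulation check.** Random-intercept REML models were fitted to complete data without covariates, 40 per arm, 600 runs per pattern, with correlation 0.7 between adjacent visits decaying as an autoregressive series. Monte Carlo error near 5% is √(0.05 × 0.95/600) = 0.9 percentage points.

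- 1.2 / 1.7 / 2: mean model SE 0.370 against 0.444 from the 6-month data alone. Rejection was 10.3%, against 6.7% with the 6-month variance.
- 2.5 / 2.2 / 2: rejection 3.0%, against 5.2% with the 6-month variance.
- 2 / 2 / 2: mean model SE 0.446, rejection 4.8%. Decaying correlation with equal variances did no harm.

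**Could variances differ even with a constant raw SD?** The model adjusts for baseline, so residual variance is what counts. Let the raw SD be 2 at every visit, with baseline correlations ρ of 0.9 / 0.7 / 0.6 (assumed). One slope for all visits is the mean correlation, b = 2.2/3 = 0.733. The residual variances 4(1 − 2bρ + b²) are 0.87, 2.04 and 2.63, with mean 1.85. So r = √(1.85/2.63) = 0.84 and type I error is 10.0%. With 0.8 / 0.7 / 0.65, r = 0.91 and type I error is 7.3%. A flat 0.7 returns 5.0%.

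**The case against.** The strongest objection is that the article never calls the patient effect the only covariance term. The name mixed model for repeated measures often denotes an unstructured residual covariance, and the phrase about patients may only mark the patient as the clustering unit. Residual structure, degrees of freedom and fallback are commonly left to a statistical analysis plan, which is not shown. This stands in part: silence about the residual structure is no fault in an article. But the sentence does name a random component. If an unstructured covariance is intended, a random intercept beside it is redundant, so the wording still deserves changing.

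A reader might infer that the primary test's standard error and type I error are wrong as planned. The documents do not support that. The standard error is right when visit variances are equal, and no visit-specific SD is given, so neither size nor direction is known. The SD of 2 belongs to the subscore and not to the residual of the change, although r depends only on relative SDs.

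The argument from baseline correlation makes rising residual variance plausible and no more. Table 1 places inclusion 24 to 48 hours after onset, but the article does not say which assessment supplies the baseline motor score.

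A reader might also expect harm from unequal correlations or from dropout. With complete data the first did none. The second may matter but was not quantified.

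**Conclusion.** The point holds conditionally. If the stated model is fitted as a random intercept with independent, equal-variance residuals, the 6-month standard error reflects the visit-averaged variance. Over the assumed patterns it runs from about 21% too small to about 17% too large, with type I error from about 12% down to about 2%. There is no error if residual variances are equal across visits.

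These figures assume complete data, 40 per arm and three post-baseline visits in the model. The estimated difference itself is not biased in that setting. The point is a cheap improvement to the primary analysis, and not a demonstrated error or a must-fix.

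**What to change.** In section 2.9, and in the analysis plan, replace the random patient effect with an unstructured within-patient covariance over the 2-week, 3-month and 6-month visits. That is 3 × 4/2 = 6 parameters, feasible with 80 patients. State Kenward–Roger degrees of freedom, and name a heterogeneous-variance fallback, such as heterogeneous Toeplitz, in case the model does not converge. Settle this before unblinding. A baseline-by-visit term is an optional refinement; leaving it out does not bias the randomised comparison.

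The cost is one sentence and a few degrees of freedom. The same sentence can serve the behavioural secondary outcomes, which section 2.9 analyses in the same way, with the visits named for each.

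### The primary model's list of allocation factors omits NIHSS severity, so some precision may be lost; validity is not affected

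*Protocol article*

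**What the plan says.** Section 2.5 of the protocol article describes the allocation: "We use a dynamic allocation method based on age, severity (NIHSS score), side of infarction, recanalization procedure (thrombectomy and/or thrombolysis), and center". That makes five factors, and the severity factor is the NIHSS score, not its motor part.

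Section 2.9 defines the primary outcome: "The primary effectiveness outcome is the change in the NIHSS motor sub-score at 6 months". It is analyzed by a mixed model for repeated measures with a patient random effect and these "fixed effects: baseline NIHSS motor score, visit, treatment, and interaction between treatment and visit". The next sentence sets the further adjustment: "Gender and stratification variables for randomization (age, recanalization procedure, lesion side, and center) in the model will be adjusted". The parenthesis names four of the five allocation factors.

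The inclusion criteria show how the two scores relate: "NIHSS score ≥7, including motor score (upper and lower limbs and hands) ≥3". The motor score is a component, and two patients with equal motor scores can differ in the rest of the NIHSS.

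Section 2.9 also sends the secondary behavioral outcomes and the MRI biomarkers to the same kind of model. Whatever covariate list the primary model uses is therefore likely to be inherited by them.

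**The concern.** The two sections do not match. Section 2.9 says it adjusts for the variables used in the randomization, then gives a list that leaves one of them out. A programmer following the list would omit severity; one following the phrase before it would include it. The choice should not be left open until data are seen.

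The statistical reason to align the two is efficiency. Severity is known for every randomized patient because the allocation needs it. If total NIHSS predicts 6-month motor change beyond what the baseline motor score predicts, leaving it out leaves explainable variation in the residual. In a trial of 80 patients even a modest gain is worth having when it costs no data collection.

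**Working it through.** **1. The plan's own figure.** Section 2.4 states: "Assuming a mean NIHSS motor subscore of 3.5 in the control group and a common standard deviation of 2", and that "a sample size of 39 patients per group achieves 90% power to reject the null hypothesis of equal means", two-sided alpha 0.05, equal-variance t-test. The treatment difference is not given. Solving backwards, 39 per group at 90% power implies a difference of about 1.5. With 1.5 and SD 2, the noncentral t calculation gives 89.7% power at 38, 90.5% at 39 and 91.2% at the 40 per group to be enrolled. The figure reproduces under that assumed difference. It uses no covariates, so the omission does not undermine it.

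**2. The lists side by side.**

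| Allocation factor (2.5) | In the primary model (2.9)? |
|---|---|
| Age | Yes |
| Side of infarction | Yes |
| Recanalization | Yes |
| Center | Yes |
| Severity (NIHSS score) | No; only the baseline motor score, a component |

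**3. Size of the possible precision gain.** Let R² be the share of residual variance that total NIHSS explains once the motor score and the other covariates are in the model. This is an assumption; the documents give no value. Ignoring small chance correlation with treatment:

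SE with total NIHSS = SE without × √(1 − R²)

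- R² = 0: no reduction
- R² = 5%: 1 − √0.95 = 2.5% reduction
- R² = 10%: 1 − √0.90 = 5.1% reduction
- R² = 15%: 1 − √0.85 = 7.8% reduction

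In power terms, take 40 per group, a difference of 1.5 and a residual SD of 2 before total NIHSS is added. Power moves from 91.2% to 92.2%, 93.5% or 95.1% for partial correlations of 0.2, 0.3 or 0.4 (R² = 4%, 9% or 16%).

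**4. Simulation of the planned covariates.** N = 80, minimization on the five factors, motor score in both models, one post-baseline visit, 4,000 runs per scenario. Assumed inputs are the motor–total correlation ρ and the coefficients of the two scores (b_m, b_t, outcome scaled to variance 1). The implied R² is b_t²(1 − ρ²) / [b_t²(1 − ρ²) + residual variance], where residual variance = 1 − (b_m² + b_t² + 2·b_m·b_t·ρ). For ρ = 0.7, b_m = 0.4, b_t = 0.3 this is 0.0459 / (0.0459 + 0.582) = 7.3%. Columns 3 to 6 are the runs with no treatment effect.

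| ρ, b_m, b_t | Implied R² | Mean SE, omitted | Mean SE, included | Ratio | Type I error, omitted | Power, omitted / included |
|---|---|---|---|---|---|---|
| 0.7, 0.5, 0 | 0% | 0.4018 | 0.4041 | 0.994 | 5.3% | 96.4% / 96.2% |
| 0.7, 0.5, 0.15 | 1.8% | 0.3684 | 0.3672 | 1.003 | 5.2% | 97.9% / 97.9% |
| 0.8, 0.5, 0.2 | 2.6% | 0.3477 | 0.3455 | 1.006 | 5.3% | 98.8% / 99.0% |
| 0.7, 0.4, 0.3 | 7.3% | 0.3674 | 0.3556 | 1.033 | 5.7% | 97.7% / 98.3% |
| 0.5, 0.4, 0.3 | 9.7% | 0.3882 | 0.3707 | 1.047 | 4.6% | 97.1% / 97.7% |

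Monte Carlo error on the type I rates is about 0.7 points. Power differs by at most about 0.7 points, partly because SD 2 is here the SD before any covariate, so power is already near its ceiling. When total NIHSS adds nothing, including it raises the SE by about 0.6% (0.4041 / 0.4018).

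**5. Second simulation at R² = 5%, 10% and 15%.** Biased-coin probability 0.8, severity split at the median, ρ from 0.5 to 0.8, 6,000 runs per scenario, motor score in the model. Without total NIHSS, type I error was 4.7% to 4.9%, 4.4% to 5.0% and 4.3% to 5.0%. The model SE was 0.995 to 1.017 times the true SD of the estimate. Adding total NIHSS cut the model SE by about 2%, 5% and 7%, in line with step 3.

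**The case against.** The strongest defense is that severity is not absent. The baseline motor score is in the model, it is part of the NIHSS, and it is the baseline of the outcome itself. Only the non-motor remainder is missing, and nothing in the article shows that it predicts motor recovery. This stands, and it is why the point is small. It does not remove the mismatch: the article nowhere says that the motor score stands in for the NIHSS allocation factor.

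Two stronger readings are tempting.

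A reader might infer that the standard errors are too wide and the test conservative, because allocation balances a factor the model ignores. The formula 2Φ(−1.96/√(1 − R²)) gives levels of 4.4%, 3.9% and 3.4% for R² of 5%, 10% and 15%. It assumes perfect balance on the part of NIHSS that the motor score does not explain. Dynamic allocation over five factors, nine centers and 80 patients does not deliver that, and in simulation the level stayed near 5%. A clear excess appeared only when the motor score was dropped too and total NIHSS was prognostic beyond it (mean SE 0.46 against a true SD of 0.42 to 0.43, type I error 3.3% to 3.8%). That is not the planned model.

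A reader might also object that the simple tests in section 2.9 ("test for continuous outcomes, the chi-squared test or Fisher's exact test for binary outcomes") ignore every allocation factor. That sentence is generic and tied to no efficacy endpoint. The same section assigns the behavioral outcomes and MRI biomarkers to the mixed model and considers ordinal logistic regression for the mRS, so little of this complaint is left.

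**Conclusion.** The inconsistency between sections 2.5 and 2.9 is plain in the text. Its consequence is a modest possible loss of precision. Type I error without total NIHSS was about 4.3% to 5.7% across both simulations, so validity is not threatened. The loss is about 2% to 8% of the standard error if total NIHSS explains a further 5% to 15% of the residual variance, and essentially nothing if it adds no prognostic information.

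The mismatch itself is certain; its size is not. The R² range, the motor–total correlation and the minimization settings are assumptions, and the simulations used one post-baseline visit, not the full repeated-measures model.

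**What to change.** Add baseline NIHSS severity to the primary mixed model, either in the form used by the allocation program or as continuous total NIHSS. Carry it into the secondary behavioral and MRI models that follow the primary one, so that the analysis matches the allocation. Name the chosen form before unblinding. If the sponsor prefers the motor score to stand in for severity, the plan should say so and give the reason.

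The cost is a change of wording and one degree of freedom (for a continuous or two-class term). No new data are needed. If total NIHSS turns out not to be prognostic, the price is an SE larger by roughly half a percent.
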